### 2.4. Randomization, Allocation Concealment, and Blinding

Randomization will be separately performed at each center by an independent statistician. The subjects will be randomly assigned to the treatment or control group in a 2 : 1 ratio using block randomization method. This ratio is chosen because it will be more ethical to assign twice the number of subjects who will take placebo to the treatment group than to allocate equal number of subjects to each group [17]. Random numbers will be generated using the PROC PLAN of SAS 9.4 (SAS Institute Inc., Cary, NC, USA) by the independent statistician. The statistician will arrange the random numbers of each center in the two types (bladder body, gallbladder body) of facial shape and send the allocation lists to an independent staff. The staff will be in charge of the 3-FSDS program operation and know the type of facial shape of each subject.

When a subject passes the screening and eligibility test, his/her face image will be taken and stored using the 3-FSDS. Subsequently, the image will be sent to the independent staff operating the 3-FSDS program; the type of facial shape will be classified by 3-dimensional facial measurement using the 3-FSDS program. After the type is determined, the staff will immediately inform an investigator of the center through e-mail whether the subject will be included in the trial considering the fixed number of subjects for each type (24 bladder body, 24 gallbladder body at each center). If the subject is included in the trial, the staff will send a random number in the allocation list arranged in sequential order in each type to the investigator of the center through e-mail. Additionally, if the fixed number of subjects of each type is already full, the staff will notify the investigator that the new subject will be excluded from the trial.

The subjects, investigators, clinical research coordinator (CRC), and clinical pharmacist will be blinded to the random allocation of the trial. Only the independent statistician will be associated with the randomization. The independent staff operating the 3-FSDS program will know only the type of facial shape not the group allocation of each subject.

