### 2.7. Outcome Measurements

#### 2.7.1. Primary Outcome

*Total Dyspepsia Symptom Scale (TDS Scale)*. The TDS scale comprises 8 items (postprandial fullness and bloating, early satiety, epigastric pain, epigastric burning, nausea, vomiting, belching, and other symptoms), with a 4-point Likert scale [17, 32]. The TDS score is the total score of 8 items. This scale will be assessed at baseline, 4 weeks, and 8 weeks.

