### 2.9. Sample Size Calculation

The formula for estimating the sample size is as follows:(1)N=nt+ncnt,the number of treatment group;nc,the number of control groupnc=12nt=Zα/2+Zβ2σ2λ+1/λμc−μt2.

A previous study demonstrated 1.57 points of improvement (*μ*_*c*_ − *μ*_*t*_ = *δ*) in the TDS scale for FD after 4 weeks of YGJT treatment compared with that after the placebo treatment [17]. The study indicated a mean standard deviation (SD = *σ*) of 2.148. In the present study, the ratio (*λ*) of the treatment group to the control group will be 2 : 1 (*λ* = 2). With a power (1 − *β*) of 80% and a significance level (*α*) of 5%, assuming *δ* = 1.57 and *σ* = 2.148, a sample size of *n*_*t*_ = 44 and *n*_*c*_ = 22 subjects will be required. Considering an assumed dropout rate of 30%, a total of 96 subjects will be needed in the current study.

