### 2.10. Statistical Analysis

An independent statistician who is blinded to group allocation will conduct statistical analysis. All data will be presented as mean ± standard deviation or number (%). Baseline characteristics of the subjects will be analyzed using chi-squared test or Fisher's exact test for categorical variables and analysis of variance (ANOVA) for continuous variables. For the efficacy analysis, two-way ANOVA will be used to compare the changes in scores of each outcome for 8 weeks between the intervention groups or the facial shape types. For the safety analysis, the chi-squared test or Fisher's exact test will be used. Both* intention-to-treat* (ITT) and* per-protocol* (PP) analyses will be performed in the current trial, and the primary analysis will be based on the ITT analysis. For the ITT analysis, a full analysis set will be used, and all subjects randomly allocated to one of the two groups, have taken at least one dose of the investigational drugs, and have reported once at least the primary outcome after the baseline will be included. Missing data will be adjusted using the last observation carried forward method. For the PP analysis, all subjects who have completed the study and have complied well with the study protocol without major protocol violations will be included. The subjects with <70% compliance will be excluded from the PP analysis. For the safety analysis, all subjects who have taken at least one dose of the investigational drugs will be included. SPSS 21.0 (IBM SPSS Statistics, New York, USA) will be used for all statistical analyses. A* P* value < .05 will be considered statistically significant.

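### The primary analysis uses LOCF on a set that requires a post-baseline TDS, with 30% dropout planned for, so the 8-week contrast can be biased in either direction

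*Protocol article*

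**What the plan says.** Section 2.10 makes the intention-to-treat analysis primary and then defines it through a full analysis set. Subjects must have been randomised, must have taken at least one dose, and must "have reported once at least the primary outcome after the baseline will be included". For gaps within that set, "Missing data will be adjusted using the last observation carried forward method". The efficacy comparison is a two-way ANOVA of changes over 8 weeks. The only other efficacy analysis named is per-protocol, which is limited to compliant completers without major violations.

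Section 2.7.1 says of the TDS: "This scale will be assessed at baseline, 4 weeks, and 8 weeks". Section 2.9 says: "Considering an assumed dropout rate of 30%, a total of 96 subjects will be needed in the current study".

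**The concern.** With two post-baseline visits, LOCF can only do one thing to the 8-week change: it enters the week-4 value as the week-8 value for everyone lost in between. That is harmless if nothing changes after withdrawal, or if the shift it causes is the same in both arms. Otherwise it moves the treatment contrast.

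Subjects lost before week 4 are handled by exclusion. On the stated schedule they have no post-baseline TDS and so do not enter the set, although it is labelled intention-to-treat. Both rules depend on events after randomisation.

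The 30% allowance in the sample size protects power, not validity. The per-protocol analysis removes the same leavers and so gives no check. What is at stake is the size of the primary effect estimate and, in some circumstances, the 5% error rate.

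**Working it through.** **Inputs from the article.** Section 2.9: δ = 1.57 ("A previous study demonstrated 1.57 points of improvement", a 4-week result), σ = 2.148 ("The study indicated a mean standard deviation (SD = *σ*) of 2.148"), ratio 2:1, 80% power, α = 5% two-sided, 30% dropout, N = 96 (64 YGJT, 32 placebo).

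**The plan's own figure.** n_c = (1.960 + 0.842)² × 2.148² × (3/2) / 1.57² = 22.04 and n_t = 44.08, which the article gives as 22 and 44. Then 66/0.7 = 94.3, and 96 fits the 2:1 ratio and the four centre-by-type cells of 24. The total reproduces. Expected dropouts are 0.30 × 96 = 28.8, that is 19.2 and 9.6 by arm if the rates are equal.

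**Assumptions.** The article gives no dropout rates by arm, no course from week 4 to week 8, and no prognosis for leavers. All of these are assumed below.

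**Late dropouts, LOCF.** Let p be the share of an arm carried forward from week 4, and d the further improvement those subjects would have shown by week 8. LOCF understates the arm's mean improvement by p × d, so

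bias in favour of YGJT = p_placebo × d_placebo − p_YGJT × d_YGJT.

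This is zero when the two products match, for instance with equal dropout and the same further change in both arms.

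Take no true effect and the same d in both arms. The standard error with 64 and 32 subjects is 2.148 × √(1/32 + 1/64) = 0.465. The type I error is approximately Φ(−1.96 + bias/0.465) + Φ(−1.96 − bias/0.465). The simulated values use 64/32, SD 2.148, a week-4 to week-8 correlation of 0.6, and at least 6,000 trials per scenario.

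| Late dropout, YGJT / placebo | d (points) | Bias | Type I error, simulated |
|---|---|---|---|
| 15% / 15% | 1 or 2 | 0 | about 5% |
| 12% / 20% | 1 | 0.08 × 1 = 0.08 | 5.8% |
| 15% / 7.5% | 1 | −0.075 × 1 = −0.08 | 5.4% |
| 10% / 30% | 0.5 | 0.20 × 0.5 = 0.10 | 5.4% |
| 10% / 30% | 1 | 0.20 × 1 = 0.20 | about 7% |
| 10% / 30% | 2 | 0.20 × 2 = 0.40 | about 13.5% |
| 30% / 10% | 2 | −0.20 × 2 = −0.40 | 12.3% |

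The approximation gives 5.5%, 7.1% and 13.8% for the three 10%/30% rows, in line with the simulation. The 10%/30% split is (6.4 + 9.6)/96 = 16.7% overall, inside the planned 30%.

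**A growing effect with equal dropout.** If the true difference rises from 0.785 at week 4 to 1.57 at week 8, the LOCF estimate is 1.57 − p × 0.785:

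- 15% lost before week 4 and 15% after: p = 0.15/0.85, estimate 1.43.
- All 30% lost after week 4: p = 0.30, estimate 1.33.

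**Early dropouts, exclusion.** Let g be the amount by which excluded leavers would have improved less than stayers in their arm. The bias is p_YGJT × g_YGJT − p_placebo × g_placebo. With a true 1.57 and g between 1.0 and 2.148 in both arms:

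- 40% YGJT and 10% placebo: 1.57 + 0.30 × g = 1.87 to 2.21.
- 25% and 40%: 1.57 − 0.15 × g = 1.42 to 1.25.
- Equal rates: 1.57, no bias.

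With no true effect, the type I error over these unequal cases is about 6% to 23%.

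**The case against.** The strongest reply is that nothing in the article shows bias will occur. It gives no reason to expect different dropout by arm, and no information on change after week 4. A reader might infer from the larger scenarios that the type I error will exceed 5%, or that the plan favours YGJT. The documents support neither. With equal dropout and a constant effect the error stays at about 5%, milder imbalances give 5.4% to 5.8%, and the sign reverses with the dropout rates. The 2-point scenario assumes further change of nearly one SD, more than the whole planned effect. All of this stands, so the point is about exposure to bias.

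A reader might also infer that everyone lost before week 4 certainly has no post-baseline TDS. The article lists scheduled assessments only. A withdrawal assessment may be in the full protocol, so that statement holds on the stated schedule and no further.

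The restriction is disclosed: the article says that a full analysis set is used and lists its conditions. Further sensitivity analyses may be in an unseen analysis plan. But the article itself fixes the primary set and the LOCF rule, and extra sensitivity analyses would not change that stated choice. Finally, week 8 as the target is read from the wording on changes over 8 weeks; no single primary time point is named.

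**Conclusion.** The point holds as a conditional one. The stated primary method handles up to about 29 of 96 subjects by carrying week 4 forward or by exclusion, and no other named efficacy analysis checks the result. The contrast is biased when the late-dropout share times later change differs by arm, or when early leavers differ by arm in rate or in prognosis relative to stayers. In the assumed 10%/30% late-dropout scenarios the bias is about 0.1 to 0.4 points, at most 0.40/1.57, or about a quarter of the planned effect. With equal dropout and a growing effect, 1.57 is estimated as about 1.33 to 1.43. The early-exclusion figures rest on the assumed prognosis of leavers and are the least certain. Every size given depends on dropout splits and trajectories that the documents do not supply. This should be changed, but it does not invalidate the design.

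**What to change.** Replace LOCF as the primary method with one of the following.

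- **Constrained longitudinal mixed model.** Baseline, week-4 and week-8 TDS are all outcomes, with a common baseline mean across arms within type. Terms are visit, type, type × visit, treatment × visit, treatment × type × visit and centre, with unstructured covariance. Every randomised subject with a baseline TDS then contributes. Baseline must not also be a covariate: a model of weeks 4 and 8 only, adjusted for baseline, gets nothing from early leavers and would keep the exclusion.
- **Multiple imputation.** Impute from baseline TDS, week-4 TDS and the weekly adequate-relief answers (Section 2.7.2), then fit the planned two-way model with baseline TDS added.

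Name the week-8 treatment contrast averaged over the two facial types as primary, and use the treatment × type contrast at week 8 for the facial-type question. Keep LOCF as one sensitivity analysis and add a placebo-based imputation as another.

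The cost is a missing-at-random assumption, which the placebo-based analysis probes, and slightly more analysis work. The change is one of wording, to be made before unblinding, and N stays at 96.

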### 2.11. Quality Control

Regular monitoring will be conducted at each center by checking trial master files, informed consent forms, CRFs, compliance with treatments, AEs, and data records to ensure the accuracy and quality.

### 2.12. Ethics

The current study will be conducted in accordance with the standards of the International Committee on Harmonization of Good Clinical Practice and the revised version of the Declaration of Helsinki. The Institutional Review Board of the Kyung Hee University Korean Medicine Hospital (IRB number KOMCIRB-160115-HR-001) and the Dong-Eui University Korean Medicine Hospital (IRB number 2016-01) approved the trial protocol. This trial is registered at the Clinical Research Information Service (CRIS; KCT0001920; http://cris.nih.go.kr/cris/en/). Written informed consent will be obtained from all subjects prior to enrollment.

## 3. Discussion

This paper describes the protocol of a trial to investigate the efficacy of YGJT on FD patients classified by 3-dimensional facial measurement. This study is the first to explore the difference of the treatment effect of YGJT on FD patients classified as different types of facial shape using the 3-FSDS.

YGJT has widely been used to treat dyspeptic symptom of upper gastrointestinal diseases including FD in clinical practice in Korea, Japan, and China [8–10, 12]. A few animal and human studies have demonstrated that YGJT is effective on symptoms of FD. However, YGJT is reported to significantly improve only some symptoms of FD in clinical trials. Suzuki et al. [18] conducted a multicenter, double-blind, randomized, placebo-controlled, parallel-group trial to assess the efficacy and safety of YGJT on 247 FD patients. They showed that epigastric pain, an FD symptom, is significantly reduced by administration of YGJT. However, no significant differences were found on the proportion of patients with relief of other symptoms, such as epigastric burning, postprandial fullness, and early satiation, between the YGJT and placebo groups. In addition, a clinical trial with FD patients performed by Kusunoki et al. [20] reported that although the total score of the gastrointestinal symptom rating scale decreases after treatment with YGJT, the differences are not statistically significant. This finding may be caused by the treatment of FD, which is affected by specific constitution and type of Korean medicine diagnosis of patients. Differences of treatment effect of identical herbal medicine between FD patients with different constitutions or diagnosis types are possible. In traditional Korean medicine, particular facial characteristics have been believed to refer to assessable information related to an individual's diseases, and Hyungsang medicine has been developed as a constitutional medicine based on a Korean classical medicine literature, Donguibogam. According to the theory of Hyungsang medicine, the bladder body type has deficient qi and excessive dampness; on the other hand, the gallbladder body type has deficient Yin-blood and excessive heat. Therefore, YGJT is considered as a herbal medicine which is more effective to the bladder body type [22, 41]. Accordingly, we will examine the efficacy of YGJT on FD patients classified as bladder or gallbladder body by 3-dimensional facial measurement using the 3-FSDS.

In addition, we will evaluate the usefulness of the 3-FSDS comparing the treatment effect of YGJT, which is more effective on patients classified as the bladder than the gallbladder body in the theory of Hyungsang medicine, for FD patients classified as different facial shape types using the 3-FSDS. As mentioned above, the 3-FSDS is a diagnostic device developed to overcome the limitations of the existing methods for the facial shape diagnosis. If the symptoms of FD in this trial more significantly improve patients classified using the 3-FSDS as the bladder than the gallbladder body, then the 3-FSDS can be used to classify the different types of facial shape by 3-dimensional facial measurement.

The results of the current study are expected to demonstrate whether YGJT administration shows difference of treatment effect on FD patients depending on the facial shape types classified as bladder or gallbladder body using the 3-FSDS. If the efficacy of YGJT on FD patients classified as specific type is proven in this trial, their dyspeptic symptoms and quality of life will improve more effectively. The objective evidence for prescribing YGJT to FD patients diagnosed as specific facial shape type will also be provided with more confidence in clinical practice. In addition, if the usefulness of the 3-FSDS is verified, the 3-FSDS will be widely used in clinical practice as a device to diagnose facial shape type by 3-dimensional facial measurement more objectively. Furthermore, more objective diagnosis will aid in achieving a more effective treatment.

## Figures and Tables

**Figure 1 fig1:**
[figure not shown]
Flow chart of the trial. 3-FSDS, 3-dimensional facial shape diagnostic system; YGJT, Yukgunja-tang.

**Figure 2 fig2:**
[figure not shown]
Components of 3-dimensional facial shape diagnostic system (3-FSDS). (a) Morphues 3D, (b) Real Face, (c) Renai MEF, and (d) Renai FSD.
